### Study design

The study is a parallel group prospective double-blind Phase 3 randomised controlled trial comparing a 12-week treatment period of oral CBD (400 mg daily) (Experimental) to placebo (Control), with both groups receiving 4 sessions of manualised CBT-based counselling. Research interviews will be conducted at baseline (week 1), 3-weekly during the study intervention (weeks 4, 7, 10 and 13) and 12-weeks after the end of treatment (week 25) (Fig. 1). The study will use a modified intention-to-treat analysis. The expected number of participants is 250, of which we estimate approximately 20% (*n* = 50) will be of Indigenous background. The study will also include qualitative interviews with Indigenous Australian participants in both control and intervention groups (a total of *n* = 15–25 Indigenous Australian participants) to examine their experiences in the study.

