#### Participant numbers

Sample size calculations are based on the analysis of the primary outcome, that is, the difference between placebo and CBD groups in total number of Cannabis-free Days over the 12-week intervention period. Ferguson has suggested that the minimum effect size (Cohen’s *d*) for an effect of practical clinical significance is 0.4167 [55]. To achieve 90% power (two-tailed) and α = 0.05, a total of *N* = 250 (*n* = 125 per group) participants are needed to detect a between-group effect size of *d* = 0.41. Of the target 250 sample, it is estimated approximately 20% (*n* = 50) of the study sample (*N* = 250) will be Indigenous Australians.

Participants who discontinue study procedures after commencing study interventions (medication dispensed on Day 1) will not be replaced in the study but will be included in the modified intention-to-treat analyses. Participants enrolled and randomised, but do not commence any treatment (no medication dispensed or other clinical interventions) will not be included in the final analysis.

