#### Informed consent, randomisation and blinding

Written informed consent is obtained on Week 1, Day 1 of the study prior to the commencement of all subsequent study procedures. Consent is obtained with the site coordinator independent of treating clinicians, to minimise ‘pressure’ to participate in the study.

The randomisation schedule has been developed by an independent statistician, with eligible participants randomised in a 1:1 ratio between groups using variable block randomisation to help maintain blinding, with subjects stratified by (a) site (to achieve approximately equal numbers of active and placebo at each site) and (b) Indigenous Australian status (to allow direct between-group statistical comparisons within Indigenous Australian participants).

Participants, clinicians, and researchers involved in service delivery, data collection and analysis will remain blinded to study conditions using matched placebos manufactured by the same manufacturer. CBD and placebo will be packaged in identically labelled containers with the participant’s ID number and site. Aside from site trial pharmacists (who have no direct contact with participants), all other members of the clinical or research teams will be blinded to group allocation.

Unblinding will occur after all data are collected, entered, cleaned and the trial database has been locked. In circumstances where allocation needs to be unblinded (e.g. severe adverse event), the principal investigator will authorise the local site investigator to break the blind (via the site trial pharmacist).

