#### Primary outcomes

We will model the effects of CBD on number of cannabis free days (out of 84 days) via single-level Gaussian regression with the outcome regressed on the main covariate experimental group (placebo vs CBD). Number of cannabis-free days in the 28 days prior to baseline will be included as a covariate to control for variation in participants’ prior frequency of use entering the study. Two treatment factors that could plausibly influence the primary outcomes and which vary across participants will also be included as covariates: number of counselling sessions attended during the study period (count variable range 0–4), and whether or not NRT was taken (binary variable measured at baseline: did not undertake NRT vs undertook NRT). If residuals are distributed normally, we will report the results from this analysis. If residuals are not distributed normally, we will treat cannabis-free days/84 as a bounded count instead of a numeric variable and use aggregated binomial regression with a logit link.

We will model urinary THC-COOH levels (a continuous outcome, in ng/MoL) via random-slopes mixed-effects models with the group, time (6-level categorical ordered predictor; Weeks 1 (baseline), 4, 7, 10, 13), the group × time interaction, number of counselling sessions attended, and whether or not NRT was undertaken as the fixed factors, and participant ID as the random factor.

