#### Statistical methods for Indigenous Australian focussed outcomes

Indigenous Australian and non-Indigenous participants will be compared on baseline participant characteristics (e.g., age, gender, frequency of substance use, scores on quality-of-life scales) via simple regression: Gaussian for continuous measures, Logistic for binary and count variables, and multinomial logistic for multilevel categorical data. For the main study analyses, comparing the frequency of illicit cannabis use between placebo and CBD groups, all participants will be pooled and included in main analyses, irrespective of Indigenous status. However, an additional regression will be performed where Indigenous status and the interaction between Indigenous status and the study drug (Placebo vs CBD), along with the primary predictor study drug, will be included in the regression.

The study will stratify randomisation according to Indigenous status, to achieve an approximately equal number of Indigenous Australian participants on active and placebo conditions, thus requiring no additional statistical procedures beyond those outlined in the previous paragraph.

The effect of the experience of discrimination on outcomes related to cannabis use disorder will be estimated via regressing various outcomes related to cannabis use on scores on the modified Everyday Discrimination Scale (m-EDS). Two regressions will be performed for each outcome, with a different version of the m-EDS as the primary predictor in each: (i) a continuous version of the scale (i.e., total score) and (ii) a three-level categorical version of the scale (no vs low vs moderate-to-high). The outcomes that the m-EDS will be regressed on will be: (i) (baseline characteristics (e.g., years of regular cannabis use, scores on quality-of-life scales), (ii), treatment engagement (e.g., treatment retention, number of counselling sessions) and (iii) outcomes during the trial (e.g., frequency of cannabis use, health measures). As described above, the type of regression will depend on the type of outcome: Gaussian for continuous, logistic for binary or bounded count, ordinal logistic for ordered categorical, and negative binomial for unbounded count. The effect of m-EDS on treatment retention will be estimated via Kaplan Meier plots discrete-time hazard model with complementary log–log link function.

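### The fallback model for cannabis-free days is a plain aggregated binomial with no overdispersion named, so its intervals would be too narrow if it is used as written

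*Protocol article*

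**What the plan says.** Under Data analysis, Primary outcomes, the protocol article regresses the number of cannabis-free days (out of 84) on treatment group in a single-level Gaussian model. The covariates are baseline cannabis-free days, counselling sessions attended and nicotine replacement. The choice of model then depends on a residual check: "If residuals are distributed normally, we will report the results from this analysis". Otherwise, "we will treat cannabis-free days/84 as a bounded count instead of a numeric variable and use aggregated binomial regression with a logit link".

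Only the outcome type and the likelihood are said to change. No random effect, dispersion term or robust variance is named for the fallback. The next paragraph of the same section does name participant ID as a random factor, but for urinary THC-COOH. Under Secondary outcomes, that mixed-model approach is carried to the repeated measures, and unbounded counts are given a negative binomial, which allows overdispersion.

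The sample size (Participant numbers) rests on one figure per person, the "total number of Cannabis-free Days over the 12-week intervention period", with a standardised effect of 0.41 and 125 per group.

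**The concern.** An aggregated binomial with 84 trials per person takes all its variance from the mean. Given the covariates, it assumes that the 84 days are independent with a common probability of use. Cannabis use does not behave like that: some people stop, some cut down and some carry on, and a person's days resemble one another. The variance of the 84-day total between people then exceeds the binomial variance, and a model without a term for the excess reports intervals that are too narrow.

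This matters because it affects a primary endpoint. In effect the model counts 250 × 84 = 21,000 independent days where the design has 250 independent people. If the residual check fails, the reported result could exclude no effect far more often than its stated uncertainty implies. The same check also moves the natural scale of the result from a difference in days to a log odds, unless the reported summary is fixed in advance.

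**Working it through.** **The plan's own figure.** The article states: "To achieve 90% power (two-tailed) and α = 0.05, a total of" 250 "participants are needed to detect a between-group effect size of" 0.41. The two-sample normal formula with d = 0.41, two-sided alpha 0.05 and 90% power gives 126 per arm (252 in total). Power at 125 per arm is 0.90. The stated number reproduces, on the basis of one observation per person.

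**Inputs.** From the article: 84 days per person, 125 per arm, 1:1 allocation. Not given: the SD of cannabis-free days, the mean proportion p, and the within-person correlation. Assumed: SD 10 to 30 days and p 0.2 to 0.5.

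**SD that the fallback allows.** Binomial SD = √(84 p(1 − p)):
- p = 0.2: √13.44 = 3.7 days
- p = 0.3: √17.64 = 4.2 days
- p = 0.5: √21 = 4.6 days, the maximum

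**Understatement of the standard error.** Ratio r = actual SD / binomial SD. The actual error of a nominal 5% test is 2 × (1 − Φ(1.96/r)). Each cell gives r, then the error rate, before covariates:

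| Assumed SD (days) | p = 0.2 | p = 0.3 | p = 0.5 |
|---|---|---|---|
| 10 | 2.7, 47% | 2.4, 41% | 2.2, 37% |
| 15 | 4.1, 63% | 3.6, 58% | 3.3, 55% |
| 20 | 5.5, 72% | 4.8, 68% | 4.4, 65% |
| 25 | 6.8, 77% | 6.0, 74% | 5.5, 72% |
| 30 | 8.2, 81% | 7.1, 78% | 6.5, 76% |

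The ratio falls below 2 only if the SD is under 2 × 3.7 = 7.3 days (p = 0.2) to 2 × 4.6 = 9.2 days (p = 0.5). In terms of within-person correlation ρ, r = √(1 + 83ρ): 2.3 at ρ = 0.05, 4.2 at 0.2 and 6.5 at 0.5.

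**In days.** At SD 20 and p = 0.3, the 95% half-width for the group difference is 1.96 × 20 × √(2/125) = 5.0 days. The plain binomial would report 1.96 × 4.2 × √(2/125) = 1.0 day.

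**Plausibility of a wide spread.** The article's background cites a 20-person open-label study in which 15% reported abstinence and 30% halved their days of use. As an illustration only, put 15% of people at 0.95 cannabis-free, 15% at 0.55 and 70% at 0.15. The mean is 0.33, the between-person variance 0.0876 and p(1 − p) 0.221. So ρ = 0.0876/0.221 = 0.40, r = 5.8 and the SD is about 25 days.

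**Covariates.** Beta-binomial data were simulated with no treatment effect, 125 per arm, p = 0.3 and ρ of 0.1 to 0.5. Without a covariate the plain binomial rejected in 49% to 79% of runs. With a moderately predictive baseline covariate (latent r² 0.25), ratios were 2.7 to 6.1 and rejection 48% to 76%. With a strong one (r² 0.5, ρ 0.2 and 0.3), they were 3.2 to 4.0 and 57% to 64%. Scaling by the estimated dispersion brought rejection back to 4% to 6%. The Gaussian comparison rejected in 3.5% to 5.5%. A wider grid (p 0.2 to 0.5, SD 10 to 25) gave 38% to 77% for the plain binomial and about 4% to 8% for the Gaussian.

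**How often the switch would occur.** The article names no test or threshold, so a 5% normality test on the residuals is itself an assumption. On that basis, rejection was 98% to 100% at SD 20 or more or at low means, but only 6% to 45% at SD 10 with a mean of 0.35 to 0.5.

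**The case against.** The best defence is that the fallback is one clause in a condensed article. The term single-level is attached to the Gaussian model only, and a separate analysis plan could add a dispersion term. That stands as a limit on wording: the article does not say that overdispersion will be ignored. It does, however, name a specific family with nothing added, next to a THC-COOH model whose random factor is named. Followed as written, the rule is wrong, which is different from a detail being left out.

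A second defence is that the analysis is Bayesian. This does not help. Posterior width follows the likelihood, and ordinary regularising priors carry little weight against 21,000 nominal trials. The error rates above can be read as how often a 95% credible interval would exclude no effect.

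A reader might infer four stronger things that the documents do not support:
- **That the switch is bound to happen.** Bounded data in people using on at least 4 days a week make it likely, but at a smaller SD and a middling mean the residuals could pass.
- **That the bounded-count regressions for Indigenous-focussed outcomes share the fault.** That section says "logistic for binary or bounded count", but refers back to the earlier description, in which repeated bounded counts have mixed models. It states no single-level binomial rule.
- **That a false positive trial would follow.** The error is conditional on the switch and on an unknown SD, and THC-COOH is a second primary endpoint with a participant random factor.
- **That the reported result must become an odds ratio.** A difference in mean days can be derived from a logit model, and the article does not say which summary will be given.

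**Conclusion.** The point holds for the primary-outcome fallback as named. It leaves between-person variation beyond the binomial unmodelled and so understates uncertainty. The size rests on an SD that the documents do not give: about 2- to 8-fold in the standard error for SD 10 to 30 days and p 0.2 to 0.5 before covariates, with the upper end an extreme. A strongly predictive baseline covariate reduces the factor but did not remove the problem in simulation. The rule is also poorly directed: it would move a primary endpoint from a comparison that keeps close to nominal error at this sample size to one that does not. Treating a bounded outcome as bounded is legitimate; the fault lies in the missing dispersion.

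**What to change.** In Primary outcomes, replace the plain aggregated binomial fallback with a beta-binomial regression, or a binomial regression with a participant-level random intercept. State that under either the Gaussian or the fallback model the group effect will be reported as a difference in mean cannabis-free days, averaged over the covariates (and over the random intercept, if used), so that the estimand does not depend on the residual check.

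Optionally, keep the Gaussian model as primary whatever the residuals show, and use the overdispersed model as a sensitivity analysis.

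The cost is a sentence or two in the protocol and analysis plan, best settled before unblinding. Beta-binomial models are standard in Bayesian regression software, and no extra data or participants are needed.

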### What are suitable primary endpoints for clinical trials of CUD treatment?

A challenge in embarking on clinical trials for substance use disorder is choosing a primary endpoint. Whilst historically abstinence (cessation of all use) has often been used in cannabis treatment research, there is increasing recognition that abstinence may not be the primary goal of treatment for patients who use cannabis. A recent consensus expert panel identified suitable outcomes when undertaking clinical trials for the treatment of CUD [50], recommending primary outcomes of (a) self-reported frequency of use, using the Time Line Follow Back (TLFB) method [51]; (b) biological assessment of cannabis use, with urinalysis of the metabolite THC-COOH or oral fluid detection of THC; and (c) severity of CUD, using a structured instrument measuring DSM-5 Criteria (e.g. Mini-International Neuropsychiatric Interview (MINI) [52]). In line with these recommendations, and consistent with the previous Phase 2a RCT, we propose to use two primary endpoints to measure illicit cannabis use: (1) self-reported ‘cannabis-free days’ and (2) urinary THC-COOH, across the 12-week treatment period of the study, alongside a range of secondary outcome measures.

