## Methods

### Research hypothesis and study aims

The *research hypothesis* is that CBD, compared to placebo, will achieve statistically and clinically significant reductions in cannabis use, as measured by the number of self-reported cannabis-free days and urinary THC-COOH levels, among treatment-seeking patients with moderate-severe CUD.

The *primary aim* of the CBD-CUD study is to examine the efficacy of CBD, compared to placebo, in reducing cannabis use (as measured by self-report and quantitative measures of cannabis metabolites (THC-COOH) in urine drug screens) during treatment (Weeks 1–12) in participants seeking treatment for moderate-severe CUD, when used in combination with psychological interventions.

*Secondary aims* include examination of (i) safety, (ii) other cannabis related measures (e.g., cannabis withdrawal and cravings, cannabis-related problems); (iii) tobacco and other substance use; (iv) health and quality of life (QoL) measures, (v) patient experience measures; (vi) treatment retention rates; (vii) cognitive performance; (viii) post-treatment (Week 24) cannabis use, health outcomes and QoL measures.

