### Outcome measures

The *primary outcomes* are illicit cannabis use during the 12-week intervention period, operationalised using two endpoints:*Cannabis-free Days* over the 12-week intervention period, producing a continuous measure between days 1 and 85. Details regarding number of days of cannabis use will be collected at each research interview (baseline week 1, weeks 4, 7, 10, week 13 and 25) using the Time Line Follow Back (TLFB) approach, a reliable and validated measure of cannabis use, particularly when combined with biological assays (e.g. UDS) and confidentially reported to independent researchers^74^.*Urinary quantitative analysis of THC-COOH (creatinine adjusted)*. Urine samples will be collected at weeks 1, 4, 7, 10, 13 and 25, and analysed using liquid chromatography-tandem mass spectrometry (LCMS). As THC-COOH can remain ‘positive’ using qualitative thresholds (e.g. 20 ng/ml in LCMS assays) for more than 30 days after abstinence in chronic heavy cannabis users [58], we will analyse quantitative levels of THC-COOH (creatinine adjusted) to detect differences in cannabis use between the two study groups, replicating the approach used in the pilot RCT [29] (see below).

Secondary outcomes (Table 1) include a range of measures that relate to cannabis use (including rates of abstinence or reduced frequency of cannabis use, cannabis withdrawal and cravings, cannabis related problems, severity of CUD), safety (adverse events), health outcomes (including mental health, physical health, QoL), consumer experience of the medication, cognitive performance, other substance use and post-treatment outcomes (12 weeks after the intervention). The relationship between experiences of racial discrimination (using the modified Everyday Discrimination Scale) and outcomes for Indigenous Australians will also be explored.

**Table 1 Tab1:** Table of all primary and secondary outcome measures included in study

Domain	Name	Description of measure	Administration timepoint
**Basic**	Demographics	7 Questions: basic demographics including: age, gender, sexuality, Aboriginal and Torres Strait Islander background, education level, employment status, relationship status and living situation. Categorical data, excluding age which is discrete numeric	Research Interview: Week 1 (baseline) Day 1

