#### Secondary outcomes

All repeated measures of secondary outcomes will be modelled using the same approach as for urinary THC-COOH. That is, random slopes mixed-effects models for repeated measures regressions with group, time, the group × time interaction, number of counselling sessions attended, and whether or not NRT was taken as the fixed factors. These models will all be based on the generalised linear model, with link functions differing depending on the form of the outcome, as follows:Numeric (e.g., PROMIS-29 scores, marijuana craving questionnaire scores): Gaussian regression with identity link functionOrdinal (e.g., motivation to change cannabis use): ordinal logistic regression with logit link functionBounded count (e.g., severity of CUD) or binary (e.g., participant rating of group allocation): binomial logistic regression with logit link functionUnbounded count (e.g., adverse event count): negative binomial regression with log link function

See Table 1 for the form of each outcome measure.

Several secondary outcomes are single observations per individual. Group, number of counselling sessions attended, and whether or not NRT was taken will be the sole predictors in these models. Total abstinence from cannabis during weeks 10–13 (non-abstinent vs abstinent) and 50% increase in cannabis-free days during weeks 10–13 relative to cannabis-free days prior to baseline (< 50% reduction vs ≥ 50% reduction) will be modelled with binary logistic regression with logit link function, relative risk of adverse events during the trial period with negative binomial regression with log link function, hazard of treatment dropout via discrete-time hazard model with complementary log–log link function.

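### The THC-COOH primary model declares six time levels but lists five weeks, and it treats the week-1 sample as an outcome instead of adjusting for it

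*Protocol article*

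**What the plan says.** Under Data analysis, Primary outcomes, THC-COOH is modelled with group, "time (6-level categorical ordered predictor; Weeks 1 (baseline), 4, 7, 10, 13), the group × time interaction", counselling attendance and nicotine replacement as fixed terms, and participant as the random factor. No baseline THC-COOH covariate is listed.

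The sampling schedule under Outcome measures has six visits: "Urine samples will be collected at weeks 1, 4, 7, 10, 13 and 25".

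The section on suitable primary endpoints defines this endpoint as "urinary THC-COOH, across the 12-week treatment period of the study". The primary aim, under Research hypothesis and study aims, concerns cannabis use "during treatment (Weeks 1–12) in participants seeking treatment for moderate-severe CUD". Post-treatment use is a secondary aim in the same section.

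The cannabis-free-days model, described in the paragraph just before the THC-COOH model, does include pre-baseline cannabis-free days as a covariate.

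The THC-COOH model is also the template for other analyses: "All repeated measures of secondary outcomes will be modelled using the same approach as for urinary THC-COOH".

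**The concern.** There are two problems, both in what the article states.

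1. **The time factor contradicts itself.** With five levels, the model covers baseline and the treatment period. With six, the only candidate on the stated schedule is week 25, which lies outside the period of the primary endpoint. These are different models for a primary endpoint, and two analysts could each claim to follow the text.

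2. **Baseline is handled inefficiently, and differently in the two primary models.** With week 1 as a time level and both group and group × time in the model, the arm means at week 1 are unconstrained. Randomisation makes them equal in expectation, and the week-1 value predicts later values, so this leaves available precision unused.

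**Working it through.** **Step 1: count the levels.** Listed weeks: 1, 4, 7, 10, 13, which is five. Scheduled urine visits: those five plus week 25, which is six. The declared count matches the sampling schedule. The list matches the treatment-period endpoint. Both cannot describe the same factor.

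**Step 2: is there a stated figure to reproduce?** None for THC-COOH. The total of 250 was set for cannabis-free days: 2 × (1.960 + 1.282)² / 0.41² = 125.0, which rounds up to 126 per arm, or 252. The stated 125 per arm gives 90.0% power (normal approximation). That figure reproduces and is not touched by this point.

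**Step 3: precision.** The documents give no variance or correlation for THC-COOH, so these are assumptions: equal variance at every visit, the same within-person correlation ρ between any two visits (compound symmetry), and complete data. Variances of the between-arm contrast are in units of 2σ²/n, with four on-treatment visits (weeks 4, 7, 10, 13).

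- Post-baseline average alone: V_post = (1 + 3ρ)/4
- Average change from week 1: V_change = (1 + 3ρ)/4 + 1 − 2ρ
- Average adjusted for week 1, or with arms constrained equal at week 1: V_adj = (1 + 3ρ)/4 − ρ²

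The excess over the adjusted contrast is exactly (1 − ρ)² for change from baseline and ρ² for the post-baseline average. Neither can be negative.

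| ρ | V_post | V_change | V_adj | V_change / V_adj | V_post / V_adj |
|---|---|---|---|---|---|
| 0.3 | 0.475 | 0.875 | 0.385 | 2.27 | 1.23 |
| 0.5 | 0.625 | 0.625 | 0.375 | 1.67 | 1.67 |
| 0.7 | 0.775 | 0.375 | 0.285 | 1.32 | 2.72 |
| 0.8 | 0.850 | 0.250 | 0.210 | 1.19 | 4.05 |

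As standard errors, the change contrast is wider by a factor of √2.27 = 1.51 at ρ = 0.3 and √1.19 = 1.09 at ρ = 0.8.

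**Step 4: does this depend on compound symmetry?** With correlation decaying by visit (first-order autoregressive), V_change / V_adj is 1.047/0.461 = 2.27 at adjacent-visit correlation 0.5, 0.791/0.481 = 1.64 at 0.7, and 0.334/0.282 = 1.18 at 0.9. The direction and rough size are the same.

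**Step 5: what it means for power.** For illustration only, take a constant effect of 0.41 SD at all four visits and 125 per arm. The averaged change contrast has 93% power at ρ = 0.3 and 98% at ρ = 0.5. The adjusted average has over 99% at both. For an effect of that size the loss is modest. It matters more if the true effect is smaller or samples are missing.

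**The case against.** The strongest reply is that this is a miscount and a preference. Six may be carried over from the six-visit schedule, and the listed weeks and the stated aim both exclude week 25. Baseline as a repeated outcome is a valid, unbiased choice under randomisation. The efficiency figures rest on a correlation that the documents do not give, and at 0.8 the change contrast loses only 19%. One averaged on-treatment contrast can be computed from the joint posterior of the stated model, and an analysis plan that is not shown may name it.

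Much of this stands, and it rules out several stronger readings:

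- **That six levels must mean week 25 is in the primary model.** A miscount fits the text equally well. In a fully categorical time factor, week 25 would also have its own mean and would affect the week 4 to 13 contrasts only indirectly.
- **That the trial tests through the interaction, leaving several coefficients to compete and raising false positives.** The interaction is one of the listed fixed terms. The article says only that the analysis serves "to detect differences in cannabis use between the two study groups". It names no coefficient as the test and gives no success rule, so no error rate can be attached to it.
- **That the random effects are over-parameterised.** The text says "via random-slopes mixed-effects models with the group, time" but does not say how time is coded in the slopes, and the parameter count depends on that.

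The reply does not remove the contradiction, which is in the printed text. Nor does it recover the lost precision. Taking only the post-baseline arm difference from the stated model is also less precise than adjusting: 1.67 times the variance at ρ = 0.5 and 2.72 times at ρ = 0.7.

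**Conclusion.** The point holds in limited form. The time factor is self-contradictory, and whether week 25 belongs to the primary THC-COOH analysis cannot be settled from its wording. The model also gives up precision that the week-1 sample already provides: 1.19 to 2.27 times the variance for an averaged change from baseline, at ρ from 0.8 to 0.3. This assumes compound symmetry, equal variances and complete data. The loss is present at any correlation below 1, but its size is not known from the documents. Validity is not at issue: the stated model is unbiased under randomisation, and the planned 250 participants are unaffected. Not naming a single contrast would not be a finding by itself, since an analysis plan may do so.

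**What to change.** In Data analysis, Primary outcomes:

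1. Correct the number of time levels so that it agrees with the listed weeks. State that week 25 is not in the primary THC-COOH analysis, and analyse it as the post-treatment secondary.
2. Use weeks 4, 7, 10 and 13 as the outcome visits with week-1 THC-COOH as a covariate. Alternatively, keep week 1 in the outcome and constrain both arms to the same mean there.
3. Report the CBD-placebo difference averaged over those four visits as the THC-COOH effect.
4. Because the repeated secondary outcomes inherit this model, state for them too which weeks are in the time factor and how baseline enters.

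The cost is a wording change before unblinding. The week-1 sample is already collected, so no new data or participants are needed.
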